### Specific objectives

- Describe the average profile of healthcare resource consumption of a retrospective cohort (patients who died from malignant neoplasm) in the last 30 days of life by diagnosis and age group.

- Quantify and compare the costs of the use of healthcare resources in the cohorts of patients with and without SAIATU intervention.

- Compare quality of life in the cohorts of patients with and without SAIATU intervention.

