### SAIATU

A model will be designed to record the daily activity of SAIATU professionals, which will allow researchers to keep track of activity during the progression of the disease and throughout the grieving process.

Variables to be recorded:

- During the progression of the illness:

◦ Number of visits by SAIATU.

◦ Number of calls from SAIATU.

- During the grieving process:

◦ Number of bereavement support visits by SAIATU.

◦ Number of bereavement support calls by SAIATU.

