### Costs of care

The cost of SAIATU’s activities will be estimated by reference to budgetary information. Cost estimates for Hospitals, Primary Care, Home Hospitalisation and Palliative Care will be arrived at by multiplying costs by the quantity of resources consumed by each patient.

Where budgetary information about the activities of Hospitals, Primary Care and Home Hospitalisation is available, a calculation will be made multiplying costs by the quantity of resources consumed by each patient.

Secondary variables:

- Socio-demographic data.

- Place of death: home or hospital.

- Level of functional dependency: Karnofsky index <50.

- Characterisation of the principal carer.

- Quality of care in Palliative Care, measured according to the Palliative Outcome Scale and validated in Spanish [27].

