### Analysis of variables

The parameters will be analysed using the statistical software SPSS 15.0 for Windows.

A descriptive study will be conducted on the *consumption of healthcare resources* by subgroup in the last 30 days of life. The descriptive study will include measures of central tendency, confidence intervals at 95% for the population mean, and contingency tables (frequencies) for each of the recorded variables.

Each subgroup will be analysed by age, sex, and main diagnosis.

For the comparison of proportions, Pearson’s Χ^2^ test, or, when appropriate, Fisher’s exact test will be used to calculate relative risk (RR), absolute risk reduction (ARR) and the number needed to treat (NNT) with 95% confidence interval.

The Student T-test will be applied to calculate the equality of means for independent samples in the case of continuous variables, upon confirmation of the conditions of normality and homoscedasticity.

The quantification of costs incurred by the SAIATU program will be calculated on the basis of the activities performed by the program’s professionals, measured in hours of care. Based on the actual time spent on patients, the total cost will be distributed between each of the activities.

Calculations of unit costs per activity, taking into account the number of times each activity is performed for the period under analysis, will finally be performed.

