## Discussion

SAIATU could become a benchmark for an innovative model of home-based palliative care, focusing on the complementary aspects of healthcare; namely, social welfare and companionship. It is the first program to define a specific portfolio of services directed at the social welfare and support of end-of-life patients. This will allow the creation of new professional profiles to carry out this type of work, as well as clarifying which capabilities should be fostered in the training of in-home support staff, so that in the future they will be able to care for patients with advanced disease and high levels of dependency (a basic tool to cope with the socio-demographic changes we are currently undergoing).

The current project could be a graphic demonstration of an important solution to improved efficiency in the health system, through investment in resources outside the health system; in this case, in the social sector. Should the current hypothesis be confirmed, the creation of a reserve of appropriately trained home care professionals would lead to a more community-based model of healthcare, resulting in a more economical expenditure of the total resources used in the integrated care process.

If there is evidence of a difference between the cohorts under study, it would be possible to estimate, based on the incidence of the various diseases, the cost savings that could be achieved through a program of professional training and communal resource procurement if the project was extended the project to the entire Basque territory.

Taken as a whole, the results will allow for an analysis of how the development of skilled social resources and socio-health co-ordination, when applied to groups of end-of-life patients, strengthens the overall efficiency of both systems: healthcare and social welfare.

It is expected that the study will stratify oncological patients by iso-resource consumption, according to the average profile of end-of-life behaviour.

It will be possible to assess the consumption of healthcare resources at different levels of care, with and without the intervention of the SAIATU program, quantifying the similarities and differences both in terms of activities undertaken and in economic terms. Furthermore, it will be possible to examine if there are statistically significant differences in a study of sufficient methodological strength and robustness.

Indirectly, the study will generate:

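### SAIATU cost is to be allocated by time that the listed variables do not record, and it is left out of the stated cost comparison, which therefore cannot support conclusions on total resources

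*Protocol article*

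**What the plan says.** **How SAIATU is costed.** Under *Costs of care*, the cost of SAIATU's "activities will be estimated by reference to budgetary information". *Analysis of variables* adds that the professionals' activities are "measured in hours of care", and then: "Based on the actual time spent on patients, the total cost will be distributed between each of the activities". Unit costs per activity follow, using how often each activity was performed over a period that is not defined.

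**What is recorded.** The *SAIATU* section lists four variables: "Number of visits by SAIATU", the number of calls, "Number of bereavement support visits by SAIATU", and the number of bereavement calls. Recording is daily and runs through the illness and the bereavement. *Home hospitalisation* likewise lists visits, calls, and bereavement visits and calls.

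**What is compared.** The cost objective under *Specific objectives* is to "Quantify and compare the costs of the use of healthcare resources in the cohorts of patients with and without SAIATU intervention". The *Hypothesis* concerns efficiency in the use of healthcare resources (less hospital use, more home-based primary care) in the last 30 days of life.

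**What is to be concluded.** If the hypothesis is confirmed, the *Discussion* foresees a community-based model "resulting in a more economical expenditure of the total resources used in the integrated care process", and later speaks of the efficiency of the health and social systems together. The Discussion part of the *Abstract* speaks of the efficiency of the system as a whole.

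**The concern.** Two parts of the costing do not join up.

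First, the allocation rule needs time, and the list of variables to be recorded has none. A budget supplies a total. It does not say how the total divides between visits and calls, or between patients.

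Second, SAIATU is a paid service that only the exposed cohort receives. A comparison restricted to healthcare cost leaves out the one component that differs between the cohorts by design. If healthcare cost falls by less than SAIATU costs, total cost rises, and the stated comparison would still show a saving. The risk is that a healthcare-only saving is reported as a saving in total resources.

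A smaller point follows. Healthcare use is analysed over the last 30 days of life, but the text does not say over which period SAIATU cost is taken or whether contacts after death count.

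**Working it through.** The plan gives no cost figure, contact duration or SAIATU budget, so there is nothing to reproduce. The check sets the sections side by side and adds one illustration with assumed values.

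**1. Does the allocation follow from the recorded variables?**

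Let *B* be the SAIATU cost to be distributed, *n_v* and *n_c* the numbers of visits and calls, and *t_v* and *t_c* their mean durations. Distribution by time gives:

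- share of *B* assigned to visits = *n_v t_v* / (*n_v t_v* + *n_c t_c*)
- unit cost of a visit = *B t_v* / (*n_v t_v* + *n_c t_c*)
- unit cost of a call = *B t_c* / (*n_v t_v* + *n_c t_c*)

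The listed variables supply *n_v* and *n_c*, and the budget supplies *B*. Nothing listed supplies *t_v* or *t_c*. Only their ratio *r* = *t_v* / *t_c* matters here, and it is unknown.

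Assume equal numbers of visits and calls, so that the visit share is *r* / (*r* + 1). Take patient A with 20 visits and 5 calls and patient B with 5 visits and 20 calls, so that the cost ratio A/B is (20*r* + 5) / (5*r* + 20).

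| Assumed *r* | Visit share of *B* | Cost ratio A/B |
|---|---|---|
| 1 | 1/2 = 50% | 25/25 = 1.0 |
| 4 | 4/5 = 80% | 85/40 = 2.1 |
| 12 | 12/13 = 92% | 245/80 = 3.1 |
| 24 | 24/25 = 96% | 485/140 = 3.5 |

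Both patients have 25 contacts. The recorded counts fit every row, so they do not determine the allocation.

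**2. Which conclusion does the stated comparison support?**

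Let *H_C* and *H_E* be the mean healthcare cost per patient in the control and exposed cohorts, and *S* the mean SAIATU cost per exposed patient. The control cohort is cared for by the public health system only, so its SAIATU cost is zero.

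- Stated comparison: Δ_health = *H_C* − *H_E*
- Comparison needed for total resources: Δ_total = *H_C* − (*H_E* + *S*) = Δ_health − *S*

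The two differ by *S*, which is positive whenever the service costs anything. The article plans to quantify SAIATU cost, but no section says that it is added to the exposed cohort's cost before the cohorts are compared. Δ_health answers the *Hypothesis*. The statements on total resources, both systems and the system as a whole need Δ_total.

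**3. Which period?**

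| Item | Recorded over | Analysed or costed over |
|---|---|---|
| Healthcare use | Home Hospitalisation: its period of care, with bereavement contacts listed | Last 30 days of life |
| SAIATU | Illness and bereavement, daily | The period analysed, not defined |

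Both services can have contacts after death. Daily records allow both to be cut to the last 30 days of life, but the text does not say that SAIATU cost will be.

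**The case against.** The strongest reply has four parts.

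*The method is top-down.* A budget total is split between activity types, and counts then turn unit costs into patient costs. Durations are needed per activity type, not for every contact of every patient. The recording form is still to be designed, and an article condenses the full protocol, so hours may be on the form. This narrows the point: patient-level timing is not strictly required, and the calculation is not shown to be impossible. It does not remove it, because even the split between types needs durations and the printed list has none.

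*SAIATU cost is not ignored.* It stands under *Costs of care* with the other services, and the *General objective* mentions cost without restricting its source. A net comparison is therefore possible. That is true, but the one cost comparison written down is of healthcare resources.

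*The wide conclusions are conditional Discussion prose, not analysis rules.* That is also true. They are nevertheless tied to confirmation of a hypothesis about healthcare use, which cannot carry them.

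*A reader might infer more than the text supports.*

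- That SAIATU cost will be taken over a different period from healthcare use. No section says so: the costing period is undefined, the record is daily, and Home Hospitalisation also lists bereavement contacts.
- That efficiency cannot be shown at all. The efficiency in the *Hypothesis* can be tested on healthcare use alone.
- That palliative care cannot be costed, because "Cost estimates for Hospitals, Primary Care, Home Hospitalisation and Palliative Care" rest on quantities and no palliative care count is itemised. The *Abstract* says that palliative care data will be recorded, and an article may leave the item list to the full protocol.
- That the 4,000 € per patient in the *Background* is a break-even point for SAIATU. It is a cited saving in hospital stays from death at home, not a SAIATU effect.

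**Conclusion.** The point holds on the printed text, with moderate confidence, in two parts and one clarification.

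- The time-based allocation of SAIATU cost has no matching variable in the SAIATU list. Under the assumed duration ratios of 1 to 24, the visit share of cost runs from 50% to 96%. These values are illustrative only.
- The stated comparison supports a conclusion on healthcare resource use, but not on total resources, both systems or the system as a whole. Read as a total saving, it is too large by the mean SAIATU cost per exposed patient. The article gives neither that cost nor an expected healthcare saving, so it cannot be said whether the sign would change.
- The SAIATU costing period is undefined and should be tied to the last 30 days of life. This is an ambiguity, not a demonstrated mismatch.

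Confidence is moderate because the activity form and the full protocol are not shown and may contain the missing time field.

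**What to change.** 1. Add the duration of each contact (start and end time, or minutes) to the SAIATU activity record.
2. State the cost comparison as healthcare plus SAIATU cost per patient, by assigned cohort, over the last 30 days of life, and show healthcare-only cost beside it.
3. Report bereavement cost after death separately, for both SAIATU and Home Hospitalisation.
4. Base any statement on total or joint efficiency on the combined cost. Otherwise, limit the conclusion to healthcare resource use.

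The cost is one more field on a form still to be designed and a few sentences of text. The combined comparison uses a SAIATU cost that is to be quantified anyway. The drawback is that the apparent saving becomes smaller. The field should be in place before recording starts, since durations not noted at the time are hard to recover reliably.

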### Ethical considerations

Ethical approval for the study was given by the Clinical Research Ethics Committee of Euskadi (CRE-C) on 10 Dec 2012.

## Discussion

SAIATU could become a benchmark for an innovative model of home-based palliative care, focusing on the complementary aspects of healthcare; namely, social welfare and companionship. It is the first program to define a specific portfolio of services directed at the social welfare and support of end-of-life patients. This will allow the creation of new professional profiles to carry out this type of work, as well as clarifying which capabilities should be fostered in the training of in-home support staff, so that in the future they will be able to care for patients with advanced disease and high levels of dependency (a basic tool to cope with the socio-demographic changes we are currently undergoing).

The current project could be a graphic demonstration of an important solution to improved efficiency in the health system, through investment in resources outside the health system; in this case, in the social sector. Should the current hypothesis be confirmed, the creation of a reserve of appropriately trained home care professionals would lead to a more community-based model of healthcare, resulting in a more economical expenditure of the total resources used in the integrated care process.

If there is evidence of a difference between the cohorts under study, it would be possible to estimate, based on the incidence of the various diseases, the cost savings that could be achieved through a program of professional training and communal resource procurement if the project was extended the project to the entire Basque territory.

Taken as a whole, the results will allow for an analysis of how the development of skilled social resources and socio-health co-ordination, when applied to groups of end-of-life patients, strengthens the overall efficiency of both systems: healthcare and social welfare.

It is expected that the study will stratify oncological patients by iso-resource consumption, according to the average profile of end-of-life behaviour.

It will be possible to assess the consumption of healthcare resources at different levels of care, with and without the intervention of the SAIATU program, quantifying the similarities and differences both in terms of activities undertaken and in economic terms. Furthermore, it will be possible to examine if there are statistically significant differences in a study of sufficient methodological strength and robustness.

Indirectly, the study will generate:

- Organisational and operational protocols for programs such as SAIATU in the future.

- Work systems which utilise liaison committees for assessment and co-ordination between different levels of care and across sectors.

- Protocols for the primary assessment of the needs of end-of-life patients, which take into account both clinical and social aspects, supplementing the assessment of the illness itself with an account of patient’s degree of suffering, their level of dependence, and their social support network, thus allowing for better allocation of resources.

- Criteria for referrals between professionals of different levels, according to the needs of patients and their families.

## Abbreviations

PC: Palliative care; PCU: Palliative care unit; HH: Home hospitalisation.
